## Abstract

**Background:**

Proximal humeral fractures are common in older patients. The majority are minimally displaced and are associated with good outcomes after nonoperative treatment. Poorer outcomes are associated with displaced, multipart fractures. There is no clear benefit from surgical fracture fixation compared to nonoperative treatment. Replacement of the fractured humeral head with a hemiarthroplasty is another treatment option, but has not been shown to be clearly superior to nonoperative treatment or internal fixation. Recently, reverse total shoulder arthroplasty has been used to treat these fractures, particularly in the older population with several case series demonstrating good outcomes. No comparative trial has been performed to test the effectiveness of reverse total shoulder arthroplasty against nonoperative treatment.

**Methods/design:**

ReShAPE (Reverse Shoulder Arthroplasty for the treatment of Proximal humeral fractures in the Elderly) is a multicenter combined randomized and observational study. The primary objective is to compare pain and function 12 months post fracture using the American Shoulder and Elbow Society (ASES) score in patients aged 70 years or older with three- and four-part proximal humeral fractures treated by either reverse shoulder arthroplasty or nonoperative treatment. Secondary outcome measures will include the DASH (Disability of the Arm, Shoulder and Hand) score, the EQ-5D (EuroQol Health Survey), the EQ-VAS, pain, radiological parameters and complications.

**Discussion:**

The study will assess the effectiveness of reverse shoulder arthroplasty for complex proximal humeral fractures and thereby guide treatment of a common injury in the older population.

**Trial registration:**

World Health Organization Universal Trial Number (WHO UTN): U1111-1180-5452. Registered on 10 March 2016.

Australian and New Zealand Clinical Trials Registry (ANZCTR): 12616000345482. Registered on 16 March 2016.

**Electronic supplementary material:**

The online version of this article (doi:10.1186/s13063-017-1826-6) contains supplementary material, which is available to authorized users.

## Background

Humeral neck fractures account for 5% of fractures of the appendicular skeleton [1] and are the third commonest osteoporotic fracture [2] occurring with an incidence of 6.6 per 1000 person years [3]. There is a unipolar age distribution with most occurring in the older independent population with osteoporosis who fall from a standing height [4]. This incidence is set to increase in the next 20 years as a result of population growth and an aging population [5]. Forty-nine to 85% of proximal humeral fractures are minimally displaced and are usually treated nonoperatively with most having a good outcome regardless of comminution [4, 6, 7]. The poorer outcomes associated with displaced, multipart fractures has led surgeons to investigate operative alternatives [3, 8, 9]. Internal fixation with locking plates, which have some advantages in osteoporotic bone, have been subject to randomized trials, but have not been shown to improve outcome over nonoperative treatment [10–13]. Replacement of the fractured humeral head (hemiarthroplasty) is another treatment option, but has not been shown to be clearly superior to nonoperative treatment or plate fixation [14, 15].

Recently, reverse total shoulder arthroplasty has been used to treat these fractures, with several case series published [16–20]. This prosthetic design negates the effects of tuberosity malunion and nonunion that are common after internal fixation or hemiarthroplasty by creating a mechanical advantage for the deltoid muscle to allow active forward elevation and abduction. Studies comparing reverse total shoulder arthroplasty to hemiarthroplasty for the treatment of proximal humeral fractures have shown improved pain scores and functional outcomes after reverse shoulder arthroplasty [21, 22]. The use of reverse shoulder arthroplasty for the treatment of proximal humeral fractures is increasing [23]. Reverse shoulder arthroplasty has been reported to have a high complication rate including instability, loosening, poor rotation and radiological notching [24]. The risk of complications and prosthetic longevity limits the use of reverse shoulder arthroplasty in young patients with most prostheses being inserted in patients aged over 65 years [25].

## Methods/design

### Study objectives

We aim to test the hypothesis that in patients aged 70 years and over with three- or four-part fractures of the humeral neck, treatment with reverse total shoulder arthroplasty will result in improved shoulder pain and function 2 years post injury compared to nonoperative treatment.

### Study design

The study is a combined multicenter randomized controlled trial (RCT) combined with an observational cohort study. Eleven centers in Australia will participate. The study Consolidated Standards of Reporting Trials (CONSORT) flowchart is provided in Fig. 1. The SPIRIT Checklist is provided in Additional file 1 and the Standard Protocol Items: Recommendations for Interventional Trials (SPIRIT) diagram is provided in Fig. 2

**Fig. 1 Fig1:**
[figure not shown]
Consolidated Standards of Reporting Trials (CONSORT) flowchart

**Fig. 2 Fig2:**
[figure not shown]
Standard Protocol Items: Recommendations for Interventional Trials (SPIRIT) diagram

### Study population

Patients will be considered for the study if they are 70 years of age or older, medically fit for surgery, have a three- or four-part proximal humerus fracture according to Neer’s classification [6] (Table 1), present within 28 days after injury, and are available for follow-up for 24 months.

**Table 1 Tab1:** Neer’s classification of proximal humeral fractures and radiological inclusion criteria

Potential fracture “parts” (Neer)	Head (H), Shaft (S), Lesser tuberosity(LT), Greater tuberosity (GT)
Definition of a “part” (Neer)	>1 cm displacement or >45° rotation. Normal neck shaft angle 130°
Radiological inclusion criteria	3-part fractures: H + GT, S and LT H + LT, S and GT H, LT + GT and S H, GT, LT + S H, LT, GT + S 4-part fractures: H, LT, GT and S

Patients will be excluded if they are unable to provide consent due to limited proficiency in English or cognitive impairment (three or more errors on the Mini Mental Status Examination 6-item screening tool) [26], live in a residential aged care facility, have a pre-existing injury or condition of the affected side which severely affects the movement of the shoulder, a pathological fracture, other injury to the same upper limb requiring surgery, an open fracture, a fracture-dislocation or head-splitting fracture, a glenoid fracture, gross fracture displacement (no bony contact between humeral shaft and articular segment) or an axillary nerve palsy.

### Recruitment

Patients will be approached on presentation to a participating institution either in the emergency department or in the outpatient setting. Patients aged 70 years and over with a displaced proximal humerus fracture with tuberosity involvement will undergo a computed tomography (CT) scan with 3D reconstructions to assess the fracture configuration and to assess the number of fracture parts according to Neer’s classification [6] (Table 1). Linear measurements will be made with digital calipers. The normal neck shaft angle will be assumed to be 130°. Verbal consent will be requested to allow questioning to assess eligibility and to collect identifiable data. The fracture type will be screened against the inclusion criteria by two of the principal investigators. Patients who satisfy the study criteria will be invited to participate in the study and will receive a Participant Information Sheet (see Additional file 1). Patients who are willing to participate in the randomized trial will be asked to sign a Consent Form. Basic demographic and radiographic data will be collected for both groups to assess independent variables (age, gender, fracture type, diabetes (yes/no), smoking status (current/non), baseline shoulder function (American Shoulder and Elbow Society (ASES) score, Disability of the Arm, Shoulder and Hand (DASH) score) and baseline health (EuroQol Health Survey 5 dimensions (EQ-5D) and EuroQol Visual Analog Scale (EQ-VAS)). Patients who are unwilling to participate in the randomized trial will be offered participation in the observational study and will be provided with a separate Participant Information Sheet and Consent Form.

### Randomization

Randomization will occur immediately after consent has been gained. Randomization will occur by using a central, telephone-based automated randomization service with each site having its own access code (provided by the NHMRC Clinical Trials Center). Randomization will be stratified by site and will use minimization to adjust for gender and age (70–80 years, over 80 years).

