#### Statistical analysis

Differences in baseline characteristics (i.e., intrinsic and injury-related variables) between both intervention groups will be assessed using the Student’ s *t* test (parametric continuous data), the Mann-Whitney *U* test (nonparametric continuous data) or the chi-square test (categorical data).

Unadjusted analysis by intention-to-treat will be performed to test the difference in primary and secondary outcomes between the intervention groups. Student’ s *t* test (parametric continuous data), the Mann-Whitney *U* test (nonparametric continuous data) or the chi-square analysis (categorical data) will be used. A *p* value < 0.05 (two-sided tests) will be taken as threshold of statistical significance.

The observational arm will be analyzed separately, comparing the same treatment groups against the same outcomes using multivariable linear regression to adjust for potential confounders (age, sex, handedness, smoking, fracture type).

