## Discussion

The optimal treatment of three- and four-part fractures of the proximal humerus in older people has not yet been established. Operative treatment in the form of internal fixation or hemiarthroplasty has not been shown to be beneficial over nonoperative treatment. The design of the reverse shoulder arthroplasty has theoretical advantages in the treatment of these difficult fractures and several case series have shown good outcomes after reverse shoulder arthroplasty. However, there are no prospective RCTs comparing reverse shoulder arthroplasty to nonoperative treatment of displaced proximal humeral fractures in older people.

The ReShAPE trial will compare these treatment modalities and will guide future treatment for this common injury, potentially changing current practice.

The use of multiple different centers, variability in selection of surgical technique (approach, version, component fixation and prosthesis choice) and an observational cohort will increase the generalizability of the results. Randomization will occur only after review of the scans and after eligibility has been determined; therefore, making the two groups comparable and reducing selection bias.

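### Fracture type (three- or four-part) is known before allocation but is used neither in the minimization nor in the unadjusted randomized analysis, leaving avoidable chance imbalance in a 72-patient trial

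*Protocol article*

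**What the plan says.** - **Eligibility** (Study population). Patients must "have a three- or four-part proximal humerus fracture according to Neer’s classification", so both grades enter the trial.
- **Timing** (Recruitment; Discussion). A CT scan is used "to assess the fracture configuration and to assess the number of fracture parts according to Neer’s classification". "The fracture type will be screened against the inclusion criteria by two of the principal investigators", and this comes before the patient is invited. The Discussion confirms the order: "Randomization will occur only after review of the scans and after eligibility has been determined".
- **Allocation** (Randomization). "Randomization will be stratified by site and will use minimization to adjust for gender and age (70–80 years, over 80 years". Fracture type is not on the list.
- **Analysis** (Statistical analysis). The randomized groups are compared by intention to treat without adjustment, using a t test, Mann-Whitney test or chi-square test. The observational arm uses multivariable regression "to adjust for potential confounders (age, sex, handedness, smoking, fracture type". Fracture type is also among the baseline variables collected (Recruitment).
- **Prognosis** (abstract, Background). "Poorer outcomes are associated with displaced, multipart fractures".

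**The concern.** Fracture type is recorded for every patient before allocation, and the protocol thinks it important enough to adjust for in the observational arm. In the randomized arm it is used at neither of the two points where it could help. Allocation does not balance it, and the stated analysis does not correct for whatever imbalance arises.

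With 36 patients per arm, chance alone can give one arm noticeably more four-part fractures. If type affects the ASES score, part of the observed difference then reflects case mix. A result near the significance threshold would be open to the objection that one arm had the worse injuries. Separately, outcome variation explained by type stays in the error term and costs power.

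**Working it through.** **1. The plan's own figures.** The Sample size calculation section gives SD 13, difference 10 and 80% power; the two-sided 0.05 level is in Statistical analysis. The normal formula gives n = 2 × (1.96 + 0.8416)² × (13/10)² = 26.5, so 27 per arm; the t-based version gives 28. The stated 30 per arm gives power of 84.6% (normal) or 83.4% (t), so it is slightly generous. For loss to follow-up, 60/(1 − 0.17) = 72.3, close to the stated 72. The point does not depend on this step.

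**2. Inputs for the imbalance.** N = 72, split 36:36 (from the protocol). The four-part share is assumed at 30%, 40% or 50%, that is 22, 29 or 36 patients.

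**3. Chance imbalance at allocation.** With K four-part fractures in total, the number k in one arm is hypergeometric, and the gap in share is |2k − K|/36. For K = 36:
- Var(k) = 36 × 0.5 × 0.5 × 36/71 = 4.56, so SD(k) = 2.14.
- SD of the gap = 2 × 2.14/36 = 11.9 percentage points.

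| Assumed share | P(gap ≥ 10 points) | P(gap ≥ 15 points) |
|---|---|---|
| 30% (K = 22) | 44% | 20% |
| 40% (K = 29) | 34% | 15% |
| 50% (K = 36) | 48% | 24% |

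The 40% row is lower only because an odd K makes the smallest qualifying gap 5 patients instead of 4. Treating the arms as independent binomials gives 37–41% and 16–19%. Both calculations treat type as unrelated to site, gender and age.

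**4. Effect on the primary comparison.** Shift = gap in share × ASES difference between types. If four-part fractures score 10 or 15 points lower (assumed), a 15-point gap gives 0.15 × 10 = 1.5 or 0.15 × 15 = 2.25 points. The standard error of the treatment difference is 13 × √(2/30) = 3.36, so the shift is 0.45–0.67 standard errors, or 15–23% of the 10-point target.

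**5. What adjustment recovers.** With total SD 13, share p and ASES gap g, the within-type SD is √(169 − g²p(1 − p)). At 30 per arm (normal formula, unadjusted 84.6%):
- g = 5: about 86%.
- g = 10: SD 12.2 (p = 0.3) or 12.0 (p = 0.5), power 89–90%.
- g = 15: SD 11.0 or 10.6, power 94–95%.

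**6. What a third minimization factor recovers.** The protocol has eleven centers, so 72/11 ≈ 6.5 patients per site. Minimization was simulated with a 0.8 biased coin, 80% women, 45% over 80 and a 40% four-part share (all assumed).

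| Scheme | P(gap ≥ 10 points) |
|---|---|
| Gender and age only | about 38–40% |
| Type added, minimization run within each site | about 25–27% |
| Type added, run across sites with site as a factor | about 2–4% |

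Adding the factor alone changes unadjusted power little (about 83% to 82–87%). Adjusting for type gives about 87–95% under either scheme. With type balanced across sites but ignored in the analysis, the unadjusted t test becomes conservative: under no effect it rejected in about 2–3% of simulated trials instead of 5%, for gaps of 15 and 10 points.

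**The case against.** The strongest reply is that randomization has already dealt with this. Variation due to fracture type is part of the SD in the t test's standard error, so leaving type out does not inflate the type I error. A reader might infer from the omission that the primary result would be biased. The documents do not support that: any imbalance is due to chance. This objection stands in full.

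A reader might also infer that the protocol grades four-part fractures as worse than three-part ones. It does not. The Background contrasts displaced, multipart fractures with minimally displaced ones, and the remark in the Sample size calculation section separates two-part fractures from the rest. The confounder list belongs to the observational arm, where preference drives treatment, and it also names handedness and smoking. That list shows the protocol regards type as possibly prognostic, and no more.

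The Discussion sentence "Randomization will occur only after review of the scans and after eligibility has been determined; therefore, making the two groups comparable" might be read as a false claim that reviewing scans balances fracture types. Its subject is randomization carried out once eligibility is settled, so it is fairly read as being about selection bias. At most it is a wording note.

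Finally, baseline injury variables will be compared between arms, so an imbalance would be visible, and an adjusted sensitivity analysis may exist in a plan not shown. Visibility does not correct the estimate, however, and the randomized analysis that the article states is explicitly unadjusted.

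**Conclusion.** The point holds as a modest, avoidable weakness in design and precision. Type is known at every allocation and is used neither there nor in the stated randomized analysis. With an assumed 30–50% four-part share, a gap of at least 10 percentage points arises in about 34–48% of trials and one of at least 15 points in about 15–24%. The shift from a 15-point gap is 1.5–2.3 ASES points, under one standard error, and only if four-part fractures score 10–15 points lower. If the true difference between types is small, both the shift and the gain from acting are small. The trial is not invalidated and the sample size need not change. The case for acting is that the factor is already collected and cheap to use.

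**What to change.** 1. **Analysis.** In Statistical analysis, make the primary ASES comparison a linear model with treatment and fracture type (three- or four-part, as classified on CT at screening), and fix this before treatment-group outcomes are seen. The unadjusted comparison can be kept as supportive. The cost is one degree of freedom and no new data. This part delivers most of the gain in power.
2. **Allocation.** In Randomization, add fracture type as a minimization factor for the remaining patients. Load the type of patients already randomized so that existing imbalance counts, and run the minimization across sites with site as a factor. Run separately at about 6.5 patients per site, it would achieve little. The cost is one more question in the automated telephone service, a short amendment, a change to the algorithm during recruitment, and marginally looser balance on gender and age. The benefit shrinks as recruitment advances.
3. **Wording, optional.** In the Discussion, say that settling eligibility before randomization limits selection bias, and attribute comparability of the groups to the randomization itself.

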### Interventions

Participants who are randomized to surgery will be treated by insertion of a reverse total shoulder arthroplasty within 28 days of the date of injury. Surgical technique (approach, version, component fixation and prosthesis choice) will be left to the discretion of the treating surgeon. The glenosphere will be placed low, avoiding superior tilt. The tuberosities will be repaired using nonabsorbable sutures. Postoperatively, the arm will be placed in a shoulder immobilizer and patients will be instructed on elbow, wrist and hand exercises to commence immediately. Two weeks postoperatively, pendular exercises and passive flexion to 90° and passive external rotation to neutral will be commenced. Unrestricted passive and active assisted exercises will be allowed, graduating to active mobilization (as tolerated) at 6 weeks post surgery. Resisted range of motion exercises will be allowed after 12 weeks. A minimum of five physiotherapy contacts within 3 months of treatment will be provided.

Patients randomized to nonoperative treatment will be placed in a shoulder immobilizer. Elbow wrist and hand exercises will be allowed immediately. After 2 weeks, pendular exercises and passive flexion to 90° and passive external rotation to neutral will be commenced. Unrestricted passive and active assisted exercises will be allowed graduating to active mobilization (as tolerated) at 6 weeks. Resisted range of motion exercises will be allowed after 12 weeks. A minimum of five physiotherapy contacts within 3 months of treatment will be provided.

### Parallel observational cohort study

Patients who do not consent to be randomized will be offered participation in the observational arm of the study. Their treatment will consist of the same two treatment options as the RCT arm. Treatment will be decided by patient and surgeon preference as per usual practice at each institution. Treatment protocols, follow-up and outcome measures will be the same as the randomized arm. The outcome of this arm of the trial will be analyzed separately. The inclusion of the observational cohort will inform the generalizability of the randomized trial.

### Outcome measures

Participants will be followed up at 6 weeks, 3 months, 6 months, 1 year, 2 years, 5 years and 10 years. The outcome measures listed below will be assessed at 6 weeks, 3 months, 6 months, 1 year, 2 years, 5 years and 10 years.

The primary outcome will be the ASES (American Shoulder and Elbow Society) standardized shoulder assessment score patient self-reported section at 24 months [27]. This scoring system consists of two dimensions: pain and activities of daily living, which are both equally weighted giving a total score out of 100, with higher scores indicating less pain and better function. It has been shown to be reliable, valid and responsive in shoulder arthroplasty and fracture [28, 29]. Secondary outcome measures will include DASH (Disability of the Arm, Shoulder and Hand) score [30], the EQ-5D and the EQ-VAS, pain (verbal numerical rating scale, 0–10 points), radiological parameters and complications (repeat shoulder surgery, readmission, infection requiring treatment, neurological deficit, dislocation, death). Radiographs will be performed at each follow-up and will include a four-radiograph series: an AP view in neutral and 30° external rotation, and a transthoracic scapula “Y” view and axillary view. Radiographic parameters that will be assessed are: healing of the tuberosities (nonunion or resorption will be considered failures to heal), position of the tuberosities, scapula notching (according to the Sirveaux classification system [31]) and loosening and alignment (coronal and sagittal plane for patients treated nonoperatively). All radiographs will be assessed by two independent observers independently. In case of discrepancy the scoring will be decided by discussion.

#### Sample size calculation

Case series documenting the outcome after reverse shoulder arthroplasty have shown a standard deviation (SD) of 13 in the ASES score. The minimum important clinical difference (MICD) in ASES scores has been estimated to be 6.4–18 [28, 32]. We consider a difference of 10 to be necessary in order to justify the additional costs and risks of surgery. A total of 60 patients (30 in each group) will provide 80% power to detect a MICD of 10 points at a significance of 0.05. We aim to recruit 72 patients to allow for 17% loss to follow-up. The ASES score after reverse shoulder arthroplasty has been reported to be 68–86 (higher score being better) [33]. In a paper reporting the outcomes of two-, three- and four-part fractures (our study proposal is limited to three- and four-part fractures) treated nonsurgically the mean ASES score was 82.5 [13].

